### Adjuvant radiotherapy and chemotherapy

Adjuvant radiotherapy and chemotherapy will be delivered in accordance with National Comprehensive Cancer Network (NCCN) Clinical Guidelines [15]. Radiotherapy prescriptions and planning details are outlined above.

*Radiotherapy can be omitted* if there are no adverse pathological features (i.e. none of the following: extranodal extension, positive margins, pT3 or pT4 disease, nodal disease, or lymphovascular invasion).

*Adjuvant radiotherapy alone* is recommended for the following risk factors:

• Any node positive

• Lymphovascular invasion

• pT3 or pT4 tumor

• Close resection margins (<2 mm)

For patients with perineural invasion (PNI) alone and no other indications for radiotherapy, radiotherapy will be omitted [16].

*Adjuvant chemotherapy concurrent with radiotherapy* is required for patients with positive margins or extra-capsular extension. The chemotherapy will consist of cisplatin 100 mg/m^2^ delivered every 3 weeks, in 3-week cycles. For patients who are deemed unfit for such chemotherapy, the dose and/or schedule can be modified, or weekly carboplatin AUC 1.5 can be utilized, at the discretion of the medical oncologist.

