**Methods/Design:**

The target patient population comprises OPSCC patients who would be unlikely to require chemotherapy post-resection: Tumor stage T1-T2 with likely negative margins at surgery; Nodal stage N0-2, ≤3 cm in size, with no evidence of extranodal extension on imaging. Participants will be randomized in a 1:1 ratio between Arm 1 (RT ± chemotherapy) and Arm 2 (TORS ± adjuvant [chemo] RT). In Arm 1, patients with N0 disease will receive RT alone, whereas N1-2 patients will receive concurrent chemoradiation. In Arm 2, patients will undergo TORS along with selective neck dissections, which may be staged. Pathologic high-risk features will be used to determine the requirement for adjuvant radiotherapy +/- chemotherapy. The primary endpoint is QOL score using the M.D. Anderson Dysphagia Inventory (MDADI), with secondary endpoints including survival, toxicity, other QOL outcomes, and swallowing function. A sample of 68 patients is required.

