### Treatment plan

#### Arm 1: Radiotherapy

Intensity modulated radiotherapy (IMRT) will be used for all patients in this study. IMRT can be delivered using fixed-gantry techniques or rotational techniques (e.g. Tomotherapy or Volumetric Modulated Arc Therapy [VMAT]). Doses and fractionations are shown in Table 1.

**Table 1 T1:** Radiotherapy doses and fractionations

**Target volume**	**Radical-intent dose* (Arm 1)**	**Adjuvant dose (Arm 2)**
Gross tumor and nodes	70 Gy in 35 fractions over 7 weeks	N/A
Region of positive margins or extra-nodal extension	N/A	64 Gy in 30 fractions over 6 weeks
High-risk nodal areas (and operative bed in Arm 2)	63 Gy in 35 fractions over 7 weeks	60 Gy in 30 fractions over 6 weeks
Low-risk nodal areas	56 Gy in 35 fractions over 7 weeks	54 Gy in 30 fractions over 6 weeks

*In Arm 1, accelerated or hyperfractionated regimens may be used at the discretion of the radiation oncologist (e.g. same doses but delivered in 6 weeks).

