### Radiotherapy volume definitions

#### Arm 1

The gross tumor volume (GTV) is defined as the tumor and any nodes that are either: 1 cm or more in short axis, necrotic, PET positive (where applicable) or biopsy-proven to contain carcinoma. A 5 mm expansion will be added to create the clinical target volume (CTV) CTV70 (excluding natural boundaries of spread), with a further 5 mm to create the planning target volume (PTV) PTV70, which will be treated to a dose of 70 Gy in 35 fractions.

An optional high-risk nodal volume (CTV63) may be defined for areas of uncertainty (e.g. suspicious nodes not meeting the criteria above). A 5 mm margin will be added to create the PTV63, which will be treated to a dose of 63 Gy in 35 fractions.

A lower-risk nodal volume (CTV56) will be defined to include the standard lymphatic drainage sites. For well-lateralized, node-negative tonsillar primaries, this can be limited to the ipsilateral neck; for primaries at the tongue base, this must include both sides of the neck. For patients with a positive node, the contralateral neck must be treated. A 5 mm margin will be added to create the PTV56, which will be treated to a dose of 56 Gy in 35 fractions.

In Arm 1, accelerated or hyperfractionated regimens may be used at the discretion of the radiation oncologist (e.g. same doses but delivered in 6 weeks by delivering 5 twice-daily (BID) treatments, maximum one BID treatment per week)

#### Arm 2

The highest-risk volume (CTV64) will consist of regions of positive margins or extra-nodal extension. A 5 mm margin will be added to create the PTV64, which will be treated to a dose of 64 Gy in 30 fractions.

An intermediate-risk volume (CTV60) will be defined to include the entire tumor bed. CTV60 will also include the pathologically-positive neck. If both sides of the neck are pathologically positive, then both are treated to 60 Gy. A 5 mm margin will be added to create the PTV60, which will be treated to a dose of 60 Gy in 30 fractions.

A lower-risk nodal volume (CTV54) can be defined to include the standard lymphatic drainage sites that have not been dissected and/or low-risk dissected sites. For patients with a positive node, this will include the contralateral neck. A 5 mm margin will be added to create the PTV54, which will be treated to a dose of 54 Gy in 30 fractions.

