### Arm 2: TORS

#### TORS for the primary tumor

For patients with easily accessible oropharyngeal tumors as determined by the consulting surgeon, they will proceed directly to transoral robotic surgery. For patients where adequate transoral access is in question, they will first undergo an examination under anesthesia prior to randomization to ensure adequate exposure can be obtained.

TORS will be carried out using the da Vinci surgical robot (Intuitive Surgical, Sunnyvale, CA, USA). The spatula cautery will be used to remove the tumors with 1 cm margins. At the time of surgery circumferential margins will be taken and sent for frozen section analysis. The resection will proceed until negative margins are obtained if feasible. The learning curve for surgeons carrying out TORS resections has been demonstrated to be short for early-stage cases, likely fewer than 10 cases, with improvements in operative time (but not oncologic outcomes) evident as learning occurs [14]. As a result, surgeons will be required to have carried out at least 10 TORS operations prior to enrolling patients on this trial. If a positive or close margin is found on the final pathology from the TORS resection, an attempt to clear the margin transorally may be performed within four weeks of the original TORS resection. This can be done with or without the robot at the surgeon’s discretion.

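### The rule for omitting adjuvant radiotherapy after TORS leaves out close margins, which the next list makes an indication for radiotherapy

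*Protocol article*

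**What the plan says.** The abstract (Methods/Design) sets the principle for Arm 2: "Pathologic high-risk features will be used to determine the requirement for adjuvant radiotherapy +/- chemotherapy". The section Adjuvant radiotherapy and chemotherapy turns this into rules.

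- **Omission.** Radiotherapy can be left out "if there are no adverse pathological features (i.e. none of the following", and the list is then completed: "none of the following: extranodal extension, positive margins, pT3 or pT4 disease, nodal disease, or lymphovascular invasion".
- **Radiotherapy alone.** This is recommended for four risk factors: a positive node, lymphovascular invasion, pT3 or pT4, and "Close resection margins (<2 mm").
- **Perineural invasion.** "For patients with perineural invasion (PNI) alone and no other indications for radiotherapy, radiotherapy will be omitted".
- **Chemoradiotherapy.** This is required for positive margins or extracapsular extension.

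The section TORS for the primary tumor also deals with margins. "If a positive or close margin is found on the final pathology from the TORS resection", a further transoral attempt to clear it may be made within four weeks.

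The Arm 2 dose that goes with a radiotherapy recommendation is in Table 1, in the row "High-risk nodal areas (and operative bed in Arm 2"): 60 Gy in 30 fractions over 6 weeks. Radiotherapy volume definitions agrees: "An intermediate-risk volume (CTV60) will be defined to include the entire tumor bed".

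**The concern.** The two lists should mirror each other: a finding that calls for radiotherapy should also bar its omission. Three of the four radiotherapy-alone factors do so. The close margin does not. A patient whose only adverse finding is a margin under 2 mm is, by the definition in the omission rule, free of adverse features, and by the next list has a risk factor for which radiotherapy is recommended.

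This section is the operative treatment rule in Arm 2. A clinician who applies the omission list literally may give no radiotherapy to a patient whom the protocol elsewhere advises treating. Two sites could manage identical patients differently, and each could cite the protocol. The difference matters to the patient: the Background reports better health-related quality of life after TORS alone than after TORS with adjuvant radiation or chemoradiation, while the close-margin recommendation exists because the authors judged that margin to be a risk factor. No effect on power or on the primary endpoint is claimed.

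**Working it through.** The protocol gives no figure to reproduce here. The check compares the lists and then counts the profiles on which they collide.

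**Step 1. The lists side by side** (all from Adjuvant radiotherapy and chemotherapy).

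| Finding | Calls for radiotherapy alone | Calls for chemoradiotherapy | Bars omission |
|---|---|---|---|
| Positive node | yes | – | yes |
| Lymphovascular invasion | yes | – | yes |
| pT3 or pT4 | yes | – | yes |
| Close margin (<2 mm) | yes | – | **no** |
| Positive margin | – | yes | yes |
| Extranodal extension | – | yes | yes |

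The two treatment lists name 4 + 2 = 6 indications. The omission list holds 5 of them, and the one missing is the close margin.

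**Step 2. Is the omission list closed?** Yes. It is introduced by *i.e.*, which makes it a definition of having no adverse features and not a set of examples.

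**Step 3. Could positive margins be read to include close ones?** No, for two reasons. TORS for the primary tumor names a positive margin and a close margin as alternatives. The adjuvant section also sends them to different treatments, chemoradiotherapy for positive and radiotherapy alone for close. If positive included close, the close-margin bullet would have no use.

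**Step 4. Count the profiles.** Take nodal status (N0, N+, N+ with extranodal extension), margin (clear, close, positive), pT (1-2, 3-4) and lymphovascular invasion (no, yes): 3 × 3 × 2 × 2 = 36 profiles.

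- *As written.* Omission needs N0, pT1-2, no lymphovascular invasion and a margin that is not positive. That leaves clear or close: 1 × 2 × 1 × 1 = 2 profiles. The one with the close margin also meets the radiotherapy-alone list, so 1 profile meets both rules. No profile is left without a rule.
- *With the close margin added to the omission list.* Omission needs a clear margin: 1 × 1 × 1 × 1 = 1 profile. The overlap is 0 of 36, and still no profile is left without a rule.

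**Step 5. Does other text settle the conflict?** The perineural-invasion sentence omits radiotherapy only when there is no other indication. That supports radiotherapy as the intent for a close margin, but it does not alter the omission list. Re-resection of a close margin is optional and gives no rule if the margin stays close.

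**The case against.** The best case on the other side is that the text, read as a whole, already gives the answer. The omission rule is permissive and the close-margin rule advisory, so neither orders the opposite of the other; where the protocol wants a mandate, it uses stronger verbs. The close-margin bullet is the more specific text, carries a numeric threshold and sits directly below the omission sentence. The harm needs a clinician who stops reading before it.

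Other provisions lower the practical risk. Follow-up evaluation and assessment of efficacy has radiotherapy booked in advance for Arm 2, so omission takes an active decision. Inclusion criteria call for likely negative margins, and surgery aims at 1 cm margins with frozen sections. Adjuvant treatment is also placed under a named guideline, which may give sites the answer.

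Most of this stands, and it bears on how much the point matters. The group is narrow: Arm 2 only (34 planned patients), with a margin that stays under 2 mm and none of the features on the omission list. A careful clinician would probably give radiotherapy. None of it makes the lists agree. The guideline's content is not in the document, and a general reference to it does not reconcile two explicit lists printed beneath it. Nor does the document show how much benefit radiotherapy brings for an isolated close margin, so undertreatment here means only departure from the protocol's own recommendation.

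**Conclusion.** The point holds as an internal inconsistency in the Arm 2 treatment rule. Of six indications for adjuvant treatment, one, the margin under 2 mm, is missing from the list that bars omission of radiotherapy. The conflict arises in 1 of 36 pathology profiles: pN0, pT1-2, no lymphovascular invasion, close margin. That is also 1 of the only 2 profiles that meet the omission rule, but profiles are not frequencies. How many patients this would be cannot be derived, because the document gives no rate of isolated close margins.

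For a patient in that position the protocol supports either 60 Gy in 30 fractions over 6 weeks or no radiotherapy. The sample size of 68 is unaffected.

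The conclusion rests on reading the omission list as exhaustive and on positive and close margins being distinct, both of which the text supports. That radiotherapy is the intended choice is an inference from the specific bullet and the perineural-invasion sentence. It should be corrected, though it does not threaten the trial.

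**What to change.** In Adjuvant radiotherapy and chemotherapy, add *close resection margins (<2 mm)* to the list of features that bar omission, next to positive margins. This follows the apparent intent and makes the omission list the exact complement of the two treatment lists.

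The cost is five words in one list. Sample size, visits, dose levels and data collection do not change.

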### Follow-up evaluation and assessment of efficacy

The follow-up schedule is shown in Additional file 2: Appendix 2. Day 1 of follow-up will be the first day of radiotherapy (Arm 1) or the date of surgery (Arm 2); however, survival will be calculated from the date of randomization.

Arm 1: For patients receiving radiotherapy, they will be seen weekly during radiotherapy, and 4–6 weeks after radiotherapy, as part of routine care. A CT scan of the neck will be carried out 8–10 weeks after radiotherapy for assessment of residual disease for neck dissection, with a routine radiotherapy appointment 2 weeks after the CT scan (approximately 4 months from the start of treatment).

Arm 2: Patients will be seen approximately 2 weeks after completion of the neck dissection for routine post-operative assessment. Adjuvant radiotherapy, if required, shall begin within 6 weeks of surgery. Radiotherapy will be pre-booked to start within 6 weeks of the date of TORS to avoid unnecessary delays. During radiotherapy, routine visits will occur weekly during radiotherapy and 4–6 weeks afterward. For all patients in Arm 2, a return visit with the surgeon will occur at 3 months from the date of TORS.

Both arms: In addition to the above, patients will be seen at 3, 6, 9, 12, 15, 18, 21, 24, 30, 36, 42, 48, 54, and 60 months from first date of treatment. At each visit, a history and physical examination will be conducted (including laryngopharyngoscopy), and CTC-AE toxicities recorded. The QOL questionnaires are to be completed every 6 months except for the Patient Neurotoxicity Questionnaire (PNQ) that will be completed one year post-treatment. A chest x-ray will be completed every 6 months (except at the 12 month visit when a CT chest is undertaken). One year post-randomization, an audiogram should be performed.

For patients in both arms, a CT of the head, neck, and chest will be done at 12 months. Additional imaging or laboratory investigations should be carried out at the discretion of the oncologist, based on findings in the history or physical, and additional treatment (e.g. salvage treatment) is at the discretion of the treating physicians. During treatment, blood tests will be performed as per standard of care and highest BUN and creatinine values and lowest white blood cell, neutrophil and platelet counts will be recorded. One year post-treatment, a blood test to measure BUN, creatinine, and CBC/differential will be performed.

### Measurement of response

Survival outcomes: Overall survival will be measured as time from randomization until death from any cause, and progression-free survival as time to either progression or death, whichever occurs first.

QOL outcomes: The MDADI, EORTC scales, NDII, and VHI-10 will be measured at baseline and at 6-month intervals. PNQ will be completed at 1 year post-treatment.

Toxicity outcomes: CTC-AE toxicities will be recorded at every follow-up visit (3, 6, 9, 12, 15, 18, 21, 24, 30, 36, 42, 48, 54, and 60 months from the first date of treatment).

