### Objectives

To compare QOL after primary radiotherapy [± chemotherapy] (Arm 1) vs. TORS [± adjuvant (chemo)radiotherapy] (Arm 2) in patients with squamous cell carcinoma of the oropharynx, to compare toxicity profiles, and to conduct a non-definitive comparison of survival between the two modalities. (See Figure 1 - Study Schema and Figure 2- Timeline of Interventions)

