### Data Safety Monitoring Committee (DSMC)

The DSMC, consisting of at least one radiation oncologist, one medical oncologist, and surgical oncologist not involved in the study, will meet quarterly after study initiation to review toxicity outcomes. If any grade 3–5 toxicity is reported, the DSMC will review the case notes to determine if such toxicity is related to treatment. If the DSMC deems that toxicity rates are excessive (e.g. >5% grade 4 or 5 toxicity), then the DSMC can, at its discretion, recommend modification or cessation of the trial.

*Interim analysis*: the DSMC will conduct one interim analysis once 30 patients have been accrued and followed for 1-year. For this analysis, the DSMC will be blinded to the identity of each treatment arm, but QOL and OS data will be presented for each arm.

The DSMC will recommend stopping the trial if there is an OS difference that is statistically significant with a threshold of p < 0.001 using the log-rank test, based on the Haybittle-Peto stopping rule; this retains an overall alpha of 0.05. Furthermore, if the QOL scores among all patients are substantially different than estimated in the sample size calculation, the DSMC can recommend increasing or decreasing the target accrual in order to maintain statistical power.

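### The CTC-AE recording list starts at month 3 and the follow-up text is ambiguous about treatment-period visits, so acute clinical toxicity may not be graded systematically or equally between the arms

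*Protocol article*

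**What the plan says.** Under Objectives the protocol article undertakes "to compare toxicity profiles". Toxicity is a secondary endpoint, and CTC-AE dysphagia is also one of the measures of swallowing function.

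Measurement of response sets the collection times: "CTC-AE toxicities will be recorded at every follow-up visit (3, 6, 9, 12, 15, 18, 21, 24" and so on to month 60, counted from the first date of treatment.

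Follow-up evaluation and assessment of efficacy sets the clock: "Day 1 of follow-up will be the first day of radiotherapy (Arm 1) or the date of surgery (Arm 2". It then describes visits before month 3. For Arm 1, "they will be seen weekly during radiotherapy, and 4–6 weeks after radiotherapy, as part of routine care". Arm 2 patients are seen about two weeks after neck dissection and, if they have adjuvant RT, weekly during it and again 4–6 weeks later. For both arms it continues: "In addition to the above, patients will be seen at 3, 6, 9, 12, 15, 18, 21, 24" and so on to month 60, followed by "At each visit, a history and physical examination will be conducted (including laryngopharyngoscopy), and CTC-AE toxicities recorded". For the treatment period, the only items it names for recording are the worst renal values and blood counts.

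The DSMC section provides for quarterly meetings and case-note review of any reported grade 3–5 toxicity. It gives "e.g. >5% grade 4 or 5 toxicity" as an example of an excessive rate. The full follow-up schedule is in Additional file 2: Appendix 2, which is not shown.

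**The concern.** The Background motivates the trial by the acute and late toxicity of chemoradiation, and names mucositis and dysphagia. These arise during treatment, as do surgical complications. If the month 3 to 60 list is the whole collection schedule, the first CTC-AE entry comes after the entire RT course in Arm 1. In Arm 2 it comes after surgery, recovery and usually any adjuvant RT.

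Two things are then at stake. The between-arm toxicity comparison would mainly describe late effects. The first entry would also find the groups at different distances from treatment, so acute effects would be caught more often in some patients than in others. Grades that were never recorded cannot be recovered at the analysis stage.

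**Working it through.** **Step 1: the two sections side by side.** Measurement of response gives a closed list with nothing before month 3. The follow-up section allows two readings.
- Narrow: the sentence about each visit directly follows the month 3 to 60 list and joins CTC-AE to a physical examination with laryngopharyngoscopy. The visits before month 3 are described as routine, and what is recorded during treatment is specified separately as laboratory values. This agrees with Measurement of response.
- Broad: the month 3 to 60 visits are introduced as additional to those already described, so each visit could mean all of them. This conflicts with the list in Measurement of response.

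The narrow reading fits the text better, but the broad one cannot be excluded. Under either reading the text needs a correction.

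**Step 2: reproduce the article's own timing.** One month is taken as 4.348 weeks. The Arm 1 appointment after the post-RT CT falls at RT duration + 8 to 10 weeks + 2 weeks.
- 7-week RT (Table 1): 7 + 8 + 2 = 17 to 7 + 10 + 2 = 19 weeks, or 17/4.348 = 3.9 to 19/4.348 = 4.4 months.
- 6-week RT (allowed in the footnote to Table 1): 16 to 18 weeks, or 3.7 to 4.1 months.

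Both agree with the stated figure of about 4 months, so the calendar is understood correctly.

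**Step 3: where month 3 falls.** Month 3 is 3 × 4.348 = 13.0 weeks from first treatment. Adjuvant RT lasts 6 weeks (Table 1) and starts within 6 weeks of surgery (follow-up section). The week-4 start is an assumption, used to show a range.

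| Group | RT ends | Month 3 falls |
|---|---|---|
| Arm 1, 7-week RT | week 7 | 13.0 − 7 = 6.0 weeks after RT |
| Arm 1, 6-week RT | week 6 | 13.0 − 6 = 7.0 weeks after RT |
| Arm 2, adjuvant RT from week 6 | 6 + 6 = week 12 | 13.0 − 12 = 1.0 week after RT |
| Arm 2, adjuvant RT from week 4 (assumed) | 4 + 6 = week 10 | 13.0 − 10 = 3.0 weeks after RT |
| Arm 2, no adjuvant RT | none | 13.0 weeks after surgery |

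**Step 4: where the existing post-RT visit falls.** It takes place 4–6 weeks after RT. In Arm 1 that is weeks 11–13 (7-week course) or 10–12 (6-week course), at or just before month 3. In Arm 2 with adjuvant RT it is weeks 16–18 (week-6 start) or 14–16 (week-4 start), after month 3. The time before month 3 that the list leaves uncovered is therefore mainly that of the weekly on-RT visits in both arms and the post-operative visit in Arm 2.

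**The case against.** The strongest case against has four parts.

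- **Acute toxicity may be graded after all.** A reader might infer that CTC-AE is recorded only from month 3 and that acute toxicity escapes altogether. The documents do not support that. The wording about each visit can include the treatment-period visits, the detailed schedule is in an appendix not shown, and a month-3 entry might cover the worst grade since treatment began. The text is silent on that last point. This stands, and it limits the finding to what the literal text provides.
- **Severe events have another route.** A reader might infer that the DSMC's safety check is disabled. It is not: the committee reviews any reported grade 3–5 event with no time window, its 5% figure is only an example, and it acts at its discretion. Laboratory extremes are also captured during treatment. This stands for safety oversight. It does not supply systematic grading for a comparison between arms: it depends on events being reported, omits grades 1–2, and laboratory values do not measure mucositis, dysphagia or surgical complications.
- **The one-week figure is an extreme.** It holds only when adjuvant RT starts at the latest permitted time. This stands, so a range is given.
- **Unequal phase is inherent.** Strategies with different sequences are at different phases at any common visit, and the Analysis plan names no month-3 toxicity test. A reader might infer that a planned test is confounded; the article contains no such test. But unequal phase does harm when the month-3 entry is the first grading and records only the current state. Worst-grade recording over a common window largely removes that problem.

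**Conclusion.** The point holds in a limited form. The collection list for a compared secondary endpoint starts at month 3, the follow-up section does not clearly agree or disagree with it, and neither states the grading interval. Followed literally, the first 13.0 weeks have no systematic CTC-AE grading of clinical events. At the first listed point Arm 1 is 6.0–7.0 weeks past RT, Arm 2 patients with adjuvant RT about 1.0–3.0 weeks past it, and Arm 2 patients without RT 13.0 weeks past surgery. The risk is unequal capture of acute events, not their uniform absence.

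This rests on the narrow reading of the follow-up section, on current-grade recording (which the text neither states nor excludes), and on adjuvant RT starting between week 4 (assumed) and week 6 (the stated limit). If Appendix 2 lists CTC-AE at the treatment-period visits, the remaining fault is a contradiction with Measurement of response and the unstated grading interval. The MDADI comparison and the sample size of 68 are unaffected. The change should still be made, because data not collected cannot be restored later.

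**What to change.** 1. Reconcile Measurement of response with the follow-up section (and Appendix 2) by adding to the CTC-AE list the weekly on-RT visits in both arms, the visit 4–6 weeks after RT, and the visit about two weeks after neck dissection. All of these already take place.
2. State that every visit records the worst grade since the previous visit, with the first entry reaching back to the start of treatment.
3. Define the comparison as the worst grade per patient over a common acute window from randomization, and separately over a later window. The acute window must be long enough to cover adjuvant RT in Arm 2, which can end at week 12 after surgery, and recovery from it. A cut at 6 months is one option.

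The cost is a change to the schedule wording and the case-report form, and more data entry at existing visits. No visit is added and no treatment rule changes.
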